# IMplementing Predictive Analytics towards efficient COPD Treatments (IMPACT): protocol for a stepped-wedge cluster randomized impact study

**DOI:** 10.1186/s41512-023-00140-6

**Published:** 2023-02-14

**Keywords:** Protocol, Chronic obstructive pulmonary disease, Clinical prediction models, Decision aid, Process of care, Prescription appropriateness, Sex and gender

## Abstract

**Introduction:**

Personalized disease management informed by quantitative risk prediction has the potential to improve patient care and outcomes. The integration of risk prediction into clinical workflow should be informed by the experiences and preferences of stakeholders, and the impact of such integration should be evaluated in prospective comparative studies.

The objectives of the IMplementing Predictive Analytics towards efficient chronic obstructive pulmonary disease (COPD) treatments (IMPACT) study are to integrate an exacerbation risk prediction tool into routine care and to determine its impact on prescription appropriateness (primary outcome), medication adherence, quality of life, exacerbation rates, and sex and gender disparities in COPD care (secondary outcomes).

**Methods:**

IMPACT will be conducted in two phases. Phase 1 will include the systematic and user-centered development of two decision support tools: (1) a decision tool for pulmonologists called the ACCEPT decision intervention (ADI), which combines risk prediction from the previously developed Acute COPD Exacerbation Prediction Tool with treatment algorithms recommended by the Canadian Thoracic Society’s COPD pharmacotherapy guidelines, and (2) an information pamphlet for COPD patients (patient tool), tailored to their prescribed medication, clinical needs, and lung function. In phase 2, we will conduct a stepped-wedge cluster randomized controlled trial in two outpatient respiratory clinics to evaluate the impact of the decision support tools on quality of care and patient outcomes. Clusters will be practicing pulmonologists (*n* ≥ 24), who will progressively switch to the intervention over 18 months. At the end of the study, a qualitative process evaluation will be carried out to determine the barriers and enablers of uptake of the tools.

**Discussion:**

The IMPACT study coincides with a planned harmonization of electronic health record systems across tertiary care centers in British Columbia, Canada. The harmonization of these systems combined with IMPACT’s implementation-oriented design and partnership with stakeholders will facilitate integration of the tools into routine care, if the results of the proposed study reveal positive association with improvement in the process and outcomes of clinical care. The process evaluation at the end of the trial will inform subsequent design iterations before largescale implementation.

**Trial registration:**

NCT05309356.

**Supplementary Information:**

The online version contains supplementary material available at 10.1186/s41512-023-00140-6.

## Introduction

Chronic obstructive pulmonary disease (COPD), a progressive disorder of the airways, is one of the leading causes of mortality worldwide [1]. In 2012, COPD was responsible for an estimated three million deaths globally [1]. Over the disease course, COPD patients experience episodes of acute worsening of symptoms, called exacerbations or lung attacks [2]. These events, especially severe ones that require inpatient care, are major causes of morbidity and mortality [3, 4]. In Canada, severe exacerbations are one of the most common causes of medical hospitalizations, accounting for 93,353 hospital admissions in the 2017–2018 fiscal year [4]. Given the high health and economic burden, preventing exacerbations is a cornerstone of contemporary management of COPD and a major determinant of the choice of maintenance pharmacotherapy [5].

In current COPD management strategies and guidelines, such as those put forth by the Global Initiative for Chronic Obstructive Lung Disease (GOLD) [5] and the Canadian Thoracic Society (CTS) [6], treatment choice is based on a crude classification of the patient’s recent exacerbation history (e.g., whether the patient has been a “frequent exacerbator” in the previous 12 months). This approach, while intuitive and simplistic, has several drawbacks. First, it ignores other patient and disease characteristics that can improve the accuracy of exacerbation risk predictions, such as patients’ demographic characteristics, lung function, smoking history, and previous treatments [7]. Additionally, this method does not communicate a numerical estimate of risks, which can facilitate shared decision-making. It has been suggested that these limitations may be key reasons behind low adherence to guidelines among care providers, and low adherence to treatment among patients, as demonstrated in two recent studies in Canada [8, 9].

Precision medicine emphasizes the tailoring of disease management to patient characteristics and values to improve patient care and outcomes [10]. Clinical prediction models that objectively turn observed patient characteristics into actionable risk estimates are major enablers of precision medicine [11]. By quantifying the magnitude of risk and treatment benefit, clinical prediction models improve risk communication and informed decision-making between the patient and their care provider, potentially resulting in high satisfaction with, and adherence to, therapies [12]. However, an attractive feature of simple decision tools (e.g., frequent exacerbator definition) in the traditional patient-care provider encounter is that they can be applied without much added burden to the encounter. Historically, ease of use has been a component of clinical “sensibility” of clinical prediction models [13]. The increasing availability of electronic health records (EHR), which enable real-time data retrieval and automated risk calculation, should render the simplicity argument moot.

British Columbia (BC), a Canadian province with a publicly funded healthcare system serving a population of 5.2 million (as of 2021), is amid a major transition to a harmonized EHR platform. The *IM*plementing *P*redictive *A*nalytics towards efficient *C*OPD *T*reatments (IMPACT) study capitalizes on this window of opportunity to integrate a risk prediction model for COPD exacerbations into this EHR system for routine care and evaluate its impact on quality of care and patient outcomes. The risk prediction model of interest, named ACCEPT (*AC*ute *C*OPD *E*xacerbation *P*revention *T*ool) [14, 15], was designed specifically to address the shortcoming of previous studies and is considered the first COPD exacerbation clinical prediction model to be ready for clinical practice implementation [16].

### Objectives

The IMPACT study has two main objectives: (1) to integrate exacerbation risk prediction into routine COPD care by (a) designing a decision tool that incorporates ACCEPT and is embedded within the EHR and (b) developing an individualized informational handout for patients to address patient identified decisional needs, and (2) to determine the impact of the intervention on prescription appropriateness, medication adherence, quality of life, exacerbation rates, smoking cessation, and sex and gender disparities in COPD care.

## Methods

### Overall study design and setting

The IMPACT study will be implemented in two subsequent phases at two University of British Columbia (UBC) teaching respiratory clinics in Vancouver, BC, Canada: St. Paul’s Hospital and Vancouver General Hospital. During phase 1, we will conduct research with users to design an intervention that consists of a pulmonologist decision support tool that integrates the ACCEPT clinical prediction model into the EHR platform and an accompanying patient informational handout. When phase 1 is completed, we will conduct phase 2, a stepped-wedge randomized controlled trial (RCT) to evaluate the impact of the intervention on the process of care and on both patient-reported and clinical outcomes. The specific study design, population, and procedures for each of the two study phases are described separately in the following sections.

### Phase 1: Development of decision support tools for pulmonologist and patients

#### Study overview

Based on initial conversations with treating pulmonologists and patient partners, two tools will be developed to aid in the implementation of ACCEPT at point of care: (1) a decision support tool for pulmonologists, called the ACCEPT decision intervention (ADI), and (2) a printed informational handout for COPD patients that provides individual-specific advice given each patient’s predicted exacerbation risk and the prescribed medications (“patient tool”). Development of the ADI and the patient tool will follow the methods put forward by the International Patient Decision Aid Standards collaboration for systematic and user-centered development of decision aids [17, 18]. The development process is iterative, involves consultation with stakeholders (i.e., patients, pulmonologists, and clinic staff) throughout, and will be undertaken with integrated knowledge translation specialists in alignment with both the knowledge-to-action process model [18, 19] and the theory and frameworks comprised within the Theory and Techniques Tool (TTT) [20, 21]. Tool development will be divided into four related but distinct steps: (1) information gathering, (2) prototype building, (3) user feedback, and (4) pilot testing (Fig. 1).

**Fig. 1 Fig1:**
[figure not shown]
Steps in the decision support tool development for phase 1 of the IMPACT study. COPD, chronic obstructive pulmonary disease

#### Study population

Phase 1 study participants will fall into one of three groups: (1) pulmonologists, (2) individuals with COPD, and (3) clinic staff. Individuals with COPD will be eligible to participate if they have a diagnosis of COPD, are at least 18 years of age, and are able to speak and provide consent in English.

#### Tool development process

To ensure that the tools are relevant to the intended users, step 1 of tool development will identify the decisional needs and preferences of pulmonologists, and people with COPD, via semi-structured interviews. These decisional needs and preferences will inform the content and format of both tools. The interview guides will be developed collaboratively with subject area experts (e.g., decision scientists, specialists in smoking cessation) and intended tool users (e.g., pulmonologists, people with COPD). Interviews will be audio-recorded, and interview notes will be analyzed to identify preferred structure and content of the two tools. Specifically, at the end of each interview, the interviewer will compile a list of all content areas identified as important by the interviewee. For each tool, the list will be compiled across interviews with intended tool users. The complete list of all content areas identified will be discussed and reviewed with patient partners and pulmonologists on the study team to determine which content will be included in the study tools. Intended tool users will be recruited with the aim of maximizing variation in experience. For individuals with COPD, particular attention will be paid to diversity in age, sex, and gender, and time since diagnosis, based on feedback from our patient partners and the literature [22]. It is anticipated that between 4 and 6 pulmonologists will complete interviews, and between 10 and 20 individuals with COPD will be needed to reach saturation. Additional interviews will be conducted with clinic staff to assess the clinic workflow and assist in tool implementation.

Following the interviews, the initial prototype tools will be developed (step 2) using a collaborative process to draw on the unique skill sets and perspectives of different team members. At the center of this process will be decision scientists, integrated knowledge translation specialists, and COPD patient partners. The content and format of the tools will be derived from the semi-structured interviews and informed by the TTT [20, 21]. The TTT is an interactive resource that links specific behavior change techniques with mechanisms of action. It will be used to ensure that content is delivered in an evidence-based manner. Specific content will be developed with subject area experts on the study team (e.g., pulmonologists, smoking cessation experts) to ensure accuracy and alignment with best guidelines and practice principles. Patient partners and pulmonologists will provide input on the content and formatting before prototypes are developed, as well as provide feedback on prototypes to ensure the tools meet user needs and are easy to use and understand. Furthermore, following guidance from the International Patient Decision Aid Standards, the patient tool will target a grade 6 reading level [23].

The prototype tools will be revised and refined through cognitive interviews (step 3) [24]. Participants will be the intended tool users (i.e., pulmonologists will be interviewed for the ADI, and people with COPD will be interviewed for the patient tool). During the interviews, the relevant prototype tool will be presented to participants who will be instructed to navigate through the tool while stating their thoughts aloud. As needed during the interview, the interviewer will prompt the participant on specific aspects of the tool identified as important by the research team or previous participants. Interviews will be designed to elicit feedback on the layout, understandability of the language used, appropriateness of the content, and ease of use. When applicable, participants will be presented with previous versions of the relevant tools to assess the acceptability of potential changes based on previous participants’ suggestions. Cognitive interviews will continue until saturation is reached. For this work, saturation will be defined as no new significant concerns arising during cognitive interviews. It is anticipated that this will be reached after 5–10 interviews with each user group.

Following cognitive interviews, a preliminary evaluation of the patient tool (step 4) will be conducted. The metrics with which the tool will be evaluated will be determined in consultation with patient partners. Potential metrics include the following: knowledge, system usability [25], acceptability [26], and decisional conflict [27]. Quantitative evaluation of the ADI may be conducted after consultation with the study team. This evaluation would focus on usability and acceptability of the ADI. Results from quantitative evaluation will be shared with the study team, including intended tool users, to determine what changes, if any, are needed to the tool(s).

### Phase 2: A stepped-wedge cluster randomized control trial

#### Study design and setting

To test the effect of the intervention package (ADI and patient tool), we will conduct a prospective stepped-wedge cluster RCT. The unit of randomization will be staff pulmonologists at the two study sites. A stepped-wedge trial design was chosen for multiple reasons. First, clinical prediction model implementation studies should not randomize patients because of potential learning effects (changes in physician behavior after exposure to prediction model, even towards patients in the other group) [28]. Second, the stepped-wedge RCT is an implementation-oriented study design, since by the end of the trial all clusters will be assigned to the intervention arm.

In this trial, pulmonologists (clusters) will be assigned to treatment as usual (comparison arm) at the beginning of the study, with successive assignment to the intervention arm completed in a one-directional, staggered format. The one-way crossover from comparison to intervention will be allocated using a computerized random number generator and completed by the project manager during the first month of the study. Furthermore, due to the nature of the intervention, masking is not possible; thus, blinding will not be applied at the patient or cluster level. However, the allocation sequence will be concealed. Key study design features are shown in Fig. 2.

**Fig. 2 Fig2:**
[figure not shown]
The stepped-wedge cluster randomized trial design of the IMPACT study. Notes: Patterned cells represent run in period (1 month)

#### Study population

Since the intervention will be embedded into the EHR as a standard clinical decision support system and will be part of routine care, all staff pulmonologists at the two study sites (*n* = 28) will participate automatically in the study. However, conservatively anticipating data from the practice of four physicians will not be used for this study for various reasons, such as an extended leave; we aim to use data from 24 pulmonologists, who will comprise the study clusters. Individual patients who are referred to one of the participating pulmonologists at a study site with a physician-assigned diagnosis of COPD will be invited to participate in the clinical trial. For inclusion, individuals must be as follows: (1) a legal Canadian resident, (2) aged 18 years and older, and (3) able to understand English.

#### Intervention

The study intervention has two related components that will be developed during phase 1: (1) the ADI, which is a software decision tool integrated within the EHR platform, and (2) a patient tool, which is a tailored educational handout for COPD patients (Fig. 3). The ADI combines risk prediction from ACCEPT with the CTS definition of low versus high risk for exacerbations. Features of the ACCEPT clinical prediction model, including details of the development and validation studies, are reported elsewhere [14]. In summary, ACCEPT uses routinely collected patient characteristics to predict the rate and severity of exacerbations in patients with COPD during the next 12 months. Predictors include sex, age, weight, height, smoking status, symptom burden, lung function, history of exacerbations, cardiovascular risk (represented by the use of statins), and current COPD therapies (some predictors are optional). In external validation, the latest version of ACCEPT (version 2.0, which will be implemented in this study) had a c-statistic of 0.73 (95% *CI*: 0.71, 0.76) for detecting the occurrence of any moderate and severe exacerbations. In comparison, exacerbation history alone had an area under the curve (AUC) of 0.67 (95% *CI*: 0.64, 0.70; *p* < 0.001) [15]. In decision curve analysis, ACCEPT provided positive net benefit over the use of exacerbation history alone over a large range of risk thresholds [15]. Several of ACCEPT’s predictor values will be prepopulated from the electronic patient chart, but pulmonologists will be given the option to override these values. To be aligned with the CTS guidelines, the frequent exacerbator group will be defined as those with predicted moderate exacerbation rate ≥ 2 per year or predicted severe exacerbation rate ≥ 1 per year.

**Fig. 3 Fig3:**
[figure not shown]
IMPACT study Intervention package. ACCEPT, Acute COPD Exacerbation Prevention Tool; ADI, ACCEPT decision intervention; COPD, chronic obstructive pulmonary disease; CTS, Canadian Thoracic Society

The second component (the patient tool) will be a short, individualized patient information pamphlet. The information included in the pamphlet will be determined during phase 1 and will be tailored to each patient’s recommended treatment based on their ACCEPT score, their clinical needs, and their lung function.

#### Study outcomes

This is a complex trial, and we hypothesize that the overall benefits of the intervention will be multifaceted, including changes in the rate of under- and overtreatment, adherence to treatments, reduction in exacerbation rates, and narrowing of the known sex and gender gaps in COPD care [29, 30]. Table 1 describes the study’s primary endpoint and secondary outcomes and how each of these measures will help us to evaluate our hypotheses.

**Table 1 Tab1:** Description of study outcomes and corresponding hypotheses evaluated by the clinical trial

Outcome label	Outcome	Outcome measure	Relevant hypothesis	Rationale for selection
Primary outcome (outcome 1)	Prescription appropriateness	The clinician prescription will be considered concordant if it is the same as the prescription based on the ACCEPT recommendation (or if ACCEPT suggests more than one eligible prescription, the clinician prescription is one of them); otherwise, it will be considered discordant	Reduction in under- and overtreatment	Reclassifying individuals from high to low risk will avoid expensive therapies in patients who will not benefit from them, while reclassification from low to high risk will result in more intense therapies that will reduce exacerbation risk
Outcome 2	Medication adherence	Medication adherence will be assessed in two ways: (a) using the medication possession ratio and (b) self-reported medication adherence. (a) Medication possession ratio is defined as the ratio of the total days’ supply dispensed to the total days’ supply prescribed during the study period. (b) Self-reported adherence will be assessed using the COPD-specific beliefs about Medicines Questionnaire (BMQ) [31]. The COPD BMQ is a 15-item scale with 2 subscales assessing patients’ perceptions of their need for medicine and concerns regarding medicine	Higher adherence of patients to treatment recommendations	We hypothesize that accurate risk communication will improve the adherence of patients to the recommended treatment [32, 33]
Outcome 3	Rate of moderate/severe exacerbations	Moderate exacerbations: Any outpatient physician visit for COPD followed by filling prescriptions for antibiotic or oral corticosteroids Severe exacerbations: A hospital admission with the main discharge code of COPD	Change in rate of moderate/severe exacerbations	The departure from guideline-base care is a mixture of over- and undertreatment, and the proposed intervention is likely to reduce such departure from guidelines. Correcting undertreatment will reduce exacerbation rate, while correcting overtreatment will not materially change the rate, resulting in a net-reducing effect. In addition, improving adherence will further reduce exacerbations
Outcome 5	Impact of COPD on health status	Measured by the COPD Assessment Test (CAT) [34]. The CAT includes 8 questions scored from 0 to 5, with higher scores indicating more severe impact of COPD	Improved health status	Patient-reported outcomes are likely to be affected by a quality-improvement intervention that involves addressing low health literacy and inaccurate medication beliefs [35]
Outcome 6	Quality of life	Euro Quality of Life-5 Dimensions (EQ5D). The EQ5D is a standardized questionnaires that assess 5 dimensions of health status, each at 3 distinct levels [36]. These data will be used to track changes in patient-report quality of life over the duration of the study	Improved quality of life	Patient-reported outcomes are likely to be affected by a quality-improvement intervention that involves addressing low health literacy and inaccurate medication beliefs [35]
Outcome 7	Smoking cessation	Measured by the following questions 1. Smoking status will be assessed by asking, “Do you currently smoke cigarettes” (yes/no)? 2. Motivation to quit will be assessed using the motivation to stop smoking (MTSS) scale [37]. Participants will be asked to classify themselves into one of the following six stages: (a) I do not want to quit smoking, (b) I think I should stop smoking but do not really want to, (c) I want to stop smoking but have not thought about when, (d) I REALLY want to stop smoking and intend to in the next 3 months; (e) I want to stop smoking and hope to soon, (f) I REALLY want to stop smoking and I hope to in the next month 3. Nicotine dependence will be assessed using the Fagerström test [38]—a questionnaire made up of 7 questions, the first scored as 0 and 1 (yes/no), and the remaining 6 multiple-choice questions scored from 0 to 3. The total test score ranges from 0 to 10, with higher scores indicating more intense physical dependence on nicotine 4. Cessation methods will be assessed by asking: Which of the following methods have you tried in the last 6 months (check all that apply): (a) nicotine replacement therapy, (b) cold turkey, (c) Champix®, (d) bupropion (Wellbutrin or Zyban), and or (e) behavioral support (e.g., smokers help line, cessation support group, cessation website, smartphone app)	Improved lifestyle behaviors	While smoking cessation is recommended for all current smokers with COPD, very few are offered such an intervention. Studies have suggested that even a brief intervention can be effective on reducing exacerbation rates [39]

*ACCEPT* Acute COPD Exacerbation Prevention Tool, *BMQ* Beliefs about Medicines Questionnaire, *CAT* COPD Assessment Test, *COPD* Chronic obstructive pulmonary disease, *EQ5D* EuroQoL 5-dimension, *MTTS* Motivation to Stop Smoking scale

We chose “prescription appropriateness” as the primary endpoint because it is the process of care outcome that is most directly affected by the intervention, and it has been frequently used in trials on computerized decision support tools [33]. Prescription appropriateness will be assessed by determining the concordance between the pulmonologist- and CTS-based treatment recommendations.

Secondary clinical outcomes include medication adherence (outcome 2) and rate of moderate or severe exacerbations (outcome 3). Data for the clinical outcomes will be gathered through questionnaires and chart reviews, as well as by linking patient data to BC’s administrative health databases using a unique personal health number; these databases comprehensively capture all healthcare encounters of all legal residents in BC at an individual level, independent of payer [40]. Medication adherence will be assessed using the medication possession ratio. For outcome 3, we will apply a validated definition of moderate and severe exacerbations; moderate exacerbations will be defined as any outpatient physician visit for COPD followed by filling prescriptions for antibiotic or oral corticosteroids, and severe exacerbations will be defined as any hospital admission with the main discharge code of COPD [41].

For patient-reported outcomes, we will assess self-reported medication adherence, quality of life, and smoking cessation using follow-up questionnaire data. Self-reported medication adherence will be assessed using a specific version of Beliefs about Medicines Questionnaire (BMQ COPD), which has been shown to have excellent construct validity and to be a strong predictor of adherence behavior [42]. For determining the impact of the intervention on the patients’ health status and quality of life, we will administer two questionnaires: (1) the COPD Assessment Test (CAT) and (2) the EuroQoL 5-dimension (EQ5D). The CAT assesses the impact of COPD symptoms on a person’s daily activities [34], and the EQ5D is a validated tool used to measure a patient’s overall quality of life [36]. Smoking cessation will be assessed by determining patients’ smoking status, motivation to quit [37], physical nicotine dependence [38], and methods used to quit in the last 6 months.

For the sex and gender effects, we will address two a priori hypotheses. First, we hypothesize that gender-related effects are, over and beyond biological sex, independent predictors of exacerbation risk, and their incorporation into risk stratification can improve predictive accuracy. Second, the extent of gaps in COPD care is known to be different between men and women [30], and we hypothesize that incorporating the decision tools into clinical care will change such sex/gender gaps. Our study includes novel data collection on gender identity, institutionalized gender, including socioeconomic status that will be assessed during the initial study visit (Supplementary Material — Sect. 1).

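### Outcome 2(b) is labelled self-reported adherence, but the questionnaire assigned to it measures beliefs about medicines, so a change in beliefs could be read as better adherence

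*Protocol article*

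**What the plan says.** In the protocol article, Study outcomes, Table 1, outcome 2 is medication adherence, assessed in two ways. Part (a) is the medication possession ratio, which sets the days of medicine dispensed against the days prescribed. Part (b) is introduced with "Self-reported adherence will be assessed using the COPD-specific beliefs about Medicines Questionnaire (BMQ". The table then describes the instrument: "The COPD BMQ is a 15-item scale with 2 subscales assessing patients’ perceptions of their need for medicine and concerns regarding medicine". The hypothesis attached to outcome 2 as a whole is "Higher adherence of patients to treatment recommendations".

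The text after the table repeats that self-reported adherence is assessed with the COPD version of this questionnaire, and supports the choice by describing it as a scale "which has been shown to have excellent construct validity and to be a strong predictor of adherence behavior". The Discussion again lists self-reported adherence among the patient-reported secondary outcomes. Nowhere does the article name another self-report instrument that asks whether medicine is taken.

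**The concern.** The name of the outcome and the content of the instrument do not match. Adherence is a behaviour. The two subscales, as the article describes them, cover attitudes to medicines. A reader of the results who sees an outcome called self-reported adherence will assume that patients were asked how they take their medicine.

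The distinction matters in this trial because the intervention includes a tailored educational handout for patients, and the patients know when they have received it. Beliefs are a natural early response to information and can shift without any change in medicine-taking. With the present label and hypothesis, such a shift could be presented as evidence of higher adherence, and as a second result agreeing with the possession ratio when it answers a different question. Adherence is named in the Abstract and in the Objectives, so the claim would be a visible one.

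**Working it through.** No arithmetic applies. The question is whether the named instrument measures the named outcome, and it depends on no sample size, power or event figure. The check sets the relevant statements of the protocol article side by side.

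1. **Label.** Table 1, the text of Study outcomes and the Discussion all use the term self-reported adherence. The first two tie it explicitly to the beliefs questionnaire. It is not a single slip.

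2. **Content.** Table 1 says the subscales assess "perceptions of their need for medicine and concerns regarding medicine". Neither subject is whether a dose was taken. The article shows none of the 15 items, so this description of the subscales is the evidence. The absence of a described medicine-taking item adds little by itself.

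3. **Justification.** The questionnaire is said "to be a strong predictor of adherence behavior". A predictor of a behaviour is not a measure of it. Nor does prediction across patients establish that a change in belief brought about by an intervention is followed by a matching change in behaviour. That second step is what the adherence hypothesis would need.

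4. **Route from intervention to score.** In its rationale for outcomes 5 and 6, Table 1 refers to "a quality-improvement intervention that involves addressing low health literacy and inaccurate medication beliefs". That sentence is not written for outcome 2, and the pamphlet's content is still to be settled in phase 1. It nevertheless shows that the investigators regard medication beliefs as something the intervention addresses. Study design and setting adds that "blinding will not be applied at the patient or cluster level". The questionnaire is therefore answered by patients who know what they were given.

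5. **Comparison within the same table.** Outcome 7 asks about current smoking and, as a separate and separately named item, about motivation to quit. Behaviour and attitude are kept apart there. Outcome 2(b) has only the attitudinal element, under a behavioural name.

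6. **Reach.** Sample size calculations is built on prescription appropriateness, the primary outcome. Nothing in it uses the questionnaire or its label.

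Steps 1 to 3 establish the mismatch. Steps 4 and 5 show why it is more than a matter of terminology. Step 6 limits its consequences.

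**The case against.** The strongest reply has four parts.

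**The proxy is disclosed.** The article says openly what the subscales cover and cites support for the scale's validity and predictive value. The cited sources are not available here, so their strength cannot be judged. Using a validated correlate is a legitimate design choice. This stands as a reason to keep the questionnaire. It does not justify calling it adherence.

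**The two measures are already separate.** Table 1 lists (a) and (b) apart, no composite is defined, and the text and the Discussion place medication adherence among the clinical outcomes and the questionnaire among the patient-reported ones. This stands. A reader might infer that the questionnaire makes up half of outcome 2, but the article gives it no such weight.

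**Misreporting is a forecast.** No section says that a questionnaire difference alone would be taken as better adherence, or what would be concluded if the two measures disagreed. This also stands, so the point is that the present wording permits that reading. Table 1 ties both parts to the one adherence hypothesis and does nothing to exclude it.

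**The possession ratio is a proxy too.** It records dispensing, not medicine-taking. This is correct, and the ratio should be described in those terms. It is still closer to the behaviour, and it does not depend on what an unblinded patient reports.

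Two further inferences are tempting and should not be drawn. A reader might suppose that need and concerns run in opposite directions and would cancel in a total score. The article states neither a scoring direction nor that the subscales will be summed, and such detail is commonly left to the full protocol or analysis plan. A reader might also argue that patients who decline data linkage would have only the questionnaire as an adherence result. The article allows that opt-out but gives no rate, so no harm from the label can be sized from it.

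**Conclusion.** The concern holds as a fault of naming and interpretation. By the article's own description, outcome 2(b) measures beliefs about medicines. It is called self-reported adherence in three places and is attached to a hypothesis about adherence that it cannot test alone. A difference on it could be read as better adherence when only beliefs had changed.

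The size is modest: one of two measures under one secondary outcome, in a trial that describes itself as under-powered for several secondary outcomes. The primary outcome, the sample size and the data to be collected are untouched, and the possession ratio could expose a disagreement between belief and dispensing. The correction is still worth making, because it changes what the trial may say about adherence at almost no cost.

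The conclusion assumes that the article's description of the subscales is complete in substance, and that the full protocol does not add a separate medicine-taking instrument under this outcome.

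**What to change.** - In Table 1, in the text of Study outcomes and in the Discussion, rename outcome 2(b) as beliefs about medicines (need and concerns).
- Present it as an intermediate outcome on the path to adherence, with its own hypothesis about beliefs.
- State that a difference on this questionnaire alone does not support the hypothesis of higher adherence.
- Rest conclusions on adherence on the possession ratio, and describe it as a dispensing-based measure.

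The cost is a change of wording in three places and one adherence measure fewer. No new data, analysis model or sample size is needed. If the investigators wish to keep a self-reported adherence outcome, the alternative is to add an instrument that asks about taking medicine, at the price of extra questions for patients. The beliefs questionnaire would still need its own name.
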